#### Randomization, Sample Size, and Power Analysis

We used NCSS Statistical Software Program PASS [166] to compute the minimum detectable effect size estimates for hypotheses H1a to H1c and H2a to H2c proposed to fulfill specific aims 1 and 2, respectively. For all power analyses, we assume power=0.80, α=.05/3=.017, and 4 repeated assessments from 714 participants conservatively assuming 15% attrition. Standardized minimum detectable effect sizes range from .26 to .35. Therefore, our study will have the power to detect small to medium effects for the proposed hypotheses

#### Aim 3: Evaluate the Cost-effectiveness of Each Intervention Condition

Following the standard practice of measuring the cost-effectiveness of interventions, we will measure costs on a per-person basis. The intervention costs will include all program costs incurred for running the GED-HIVSR and MFG-HIVSR plus FEE programs and not just the savings match of the youth development account. The research costs will not be included in this study. Data on the savings match costs will be readily available from the management information system. Data on the costs of other program elements will be drawn from the project administrative records collected throughout the intervention period. In the analyses, the costs from multiple years will be adjusted for inflation, depreciation, and discounting. The outcome analyses described earlier will be used to estimate the extent to which the *Combined Intervention (MFG-HIVSR plus FEE plus GED-HIVSR)* versus *MFG-HIVSR plus FEE alone* increased particular outcomes (eg, viral suppression). The per-person costs of *MFG-HIVSR plus FEE and GED-HIVSR* and *MFG-HIVSR plus FEE alone* will then be divided by the relevant effect sizes to produce estimates of cost-effectiveness. We will calculate CIs for point estimates using two methods: Monte Carlo [167] and bootstrap [168].

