### Objectives

Although several interventions have shown promise in improving HIV treatment adherence among adolescents living with HIV [99-102], they mostly focus on adolescents living with HIV commuting daily from home. However, most school-going children in Uganda and many sub-Saharan African countries heavily impacted by HIV spend their time in boarding sections. The lack of attention to this group undermines the efforts to achieve the 95-95-95 targets in SSA. Our research finds that MFG and FEE [27,100] can improve HIV care outcomes among adolescents living with HIV. Moreover, consistent with the existing literature in SSA [33], our recent combination intervention study, Bridges, situated within Ugandan schools, points to the importance of building supportive familial and school environments for adolescents affected by HIV/AIDS, including adolescents living with HIV [112-115]. Building on prior experience and evidence of effective HIV stigma reduction strategies [40,95,98,116], we propose to examine an evidence-informed multilevel intervention called M-Suubi (the word *suubi* means hope) intervention that seeks to simultaneously address multiple barriers to HIV treatment adherence and care engagement among adolescents living with HIV attending boarding schools in Uganda. M-Suubi comprises of three study conditions: (1) Bolstered usual care consisting of literature on ART adherence promotion and stigma reduction, (2) MFG for HIV stigma reduction plus FEE (MFG-HIVSR plus FEE), and (3) group-based HIV stigma reduction for educators (GED-HIVSR). The study is guided by the HIV stigma framework [64], asset theory [117,118], and family system theory [119,120] and has the following goals:

Aim 1: examine the impact of M-Suubi on HIV viral suppression (primary outcome) and adherence to HIV treatment, including keeping appointments, pharmacy refills, pill counts, and retention in care.Aim 2: examine the effect of M-Suubi on HIV stigma (internalized, anticipated, and enacted), with secondary analyses to explore hypothesized mechanisms of change (eg, depression) and intervention mediation.Aim 3: assess the cost and cost-effectiveness of each intervention condition.Aim 4: qualitatively examine participants’ experiences with HIV stigma, HIV treatment adherence, and intervention and educators’ attitudes toward adolescents living with HIV and experiences with GED-HIVSR and program/policy implementation after training.

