In the FEE component, adolescents living with HIV will receive a youth development account with a 1:1 matched savings program at a financial institution accredited by the Bank of Uganda. Each youth development account will be opened in the adolescent’s name, with their primary caregiver as a cosigner, until the adolescent turns 18 years, at which time a cosigner will no longer be required. This is consistent with Ugandan banking law, which prohibits children aged <18 years from independently entering into a binding contract/operating a bank account. Family members and friends of adolescents living with HIV will be allowed and encouraged to contribute to this youth development account. It will be matched at a rate of 1:1 using money from the program. The match cap (maximum amount of youth contribution to be matched by the program) will be equivalent to US $20 per month or US $480 for the 24-month intervention period. During the intervention, adolescents will have direct access to both their personal savings deposited in the youth development account and the match provided by the study to pay for food, transportation to health clinics, and other necessities that may affect adherence. Matching will not be conditioned on the usual expenditure and/or savings goals dictated by programs [133,137,146]. The unconditional design recognizes that adolescents living with HIV and attending schools face competing demands (school fees, food for medication adherence, transport to clinics, etc) and that a conditional transfer may prohibit these vital expenditures, which may have implications for antiretroviral treatment adherence. In collaboration with participating financial institutions, the youth development account will be augmented with 4 sessions of financial literacy training, covering the basic principles of financial management, saving, and asset building.

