To test these 3 hypotheses, we will fit a 3-level generalized linear mixed model (LMM) with fixed effects for the study arm, time, and their interaction. Our analysis will follow an intent-to-treat approach, such that all participants are included in the analyses, irrespective of whether they have complete or incomplete outcome data. Maximum likelihood (ML) and multiple imputation (MI) procedures will be used to address missing data with sensitivity analyses. Sensitivity analyses will be performed using pattern-based MI to examine the robustness of the results under different missing data assumptions. We will use random intercepts for school/clinic ID to account for clustering of persons within schools and their affiliated clinics and include random intercepts, random slopes, and their covariance for person ID to account for clustering of repeated measurements within persons. Reflecting the binary HIV viral suppression outcome, a binomial distribution and log link will be used to fit a log-binomial model to estimate the relative risks. If the log-binomial model does not converge, we will substitute a Poisson model with robust SEs [159,160]. To maximize rigor, quasi-likelihood methods will not be used. Instead, maximum likelihood estimation via adaptive Gaussian quadrature with 15 integration points will be used to ensure stable solutions [161]. To test hypotheses H1a to H1c, we will perform 3 time-averaged comparisons of repeatedly measured observations across study arms to examine the intervention effects over the duration of the study period. As all possible comparisons among the 3 study arms will be evaluated, the α will be set at .05/3=.017 for each of these 3 planned comparisons. Any additional post hoc comparisons (eg, paired comparisons of groups at each time point) will maintain a nominal α of .05 using simulation-based step-down multiple comparison methods [114]. Our team has considerable experience fitting 3-level generalized LMMs to analyze data from our cluster randomized asset-based intervention trials [113,162].

#### Primary Analyses for Aim 2

To examine the effect of M-Suubi on HIV stigma, we hypothesize the following:

H2a: MFG-HIVSR plus FEE will have lower mean HIV stigma than control participants (bolstered usual care).H2b: MFG-HIVSR plus FEE plus GED-HIVSR will have lower mean HIV stigma than control participants.H2c: MFG-HIVSR plus FEE plus GED-HIVSR will have lower mean HIV stigma than MFG-HIVSR plus FEE.

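### Aim 3 divides whole-arm costs by undefined effect sizes and never forms the incremental cost-effectiveness ratio for adding the educator component

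*Protocol article*

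**What the plan says.** The Objectives section sets Aim 3 as to "assess the cost and cost-effectiveness of each intervention condition". The Aim 3 section then describes the calculation in three steps.

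- **Costs.** It says "we will measure costs on a per-person basis" and "The intervention costs will include all program costs incurred for running the GED-HIVSR and MFG-HIVSR plus FEE programs", with the savings match as one part of the total.
- **Effect.** It says "The outcome analyses described earlier will be used to estimate the extent to which the" combined intervention, set against MFG-HIVSR plus FEE alone, improved outcomes such as viral suppression. No other contrast is named in this section.
- **Ratio.** The per-person costs of the combined arm and of MFG-HIVSR plus FEE alone "will then be divided by the relevant effect sizes to produce estimates of cost-effectiveness". Intervals come from Monte Carlo and bootstrap methods.

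For viral suppression, the Aim 1 analysis specifies that a "log link will be used to fit a log-binomial model to estimate the relative risks", with a Poisson fallback. The description of Treatment Arm 2 says that this arm receives everything in Treatment Arm 1 plus GED-HIVSR, and that its purpose is to test what the school-level component adds.

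**The concern.** A cost-effectiveness ratio compares two options: the difference in cost over the difference in effect. Here the numerators are whole-arm costs, while the only effect named is a difference between the two intervention arms. Numerator and denominator therefore do not refer to the same comparison.

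At stake is the question for which the third arm exists: is it worth adding educator training to a family and economic package? If the package's cost is loaded onto the educator component, that component can look several times dearer than it is. The scale matters too. A cost divided by a relative risk is not a cost per suppressed adolescent.

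**Working it through.** **Notation.** X = per-person cost of MFG-HIVSR plus FEE. G = added per-person cost of GED-HIVSR. d1 = risk difference in suppression, MFG-HIVSR plus FEE against control. d2 = risk difference, combined against MFG-HIVSR plus FEE.

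**The plan's own figure.** The only cost figure given is the cap on the savings match, "equivalent to US $20 per month or US $480 for the 24-month intervention period". It reproduces: 20 × 24 = 480. (The Study Overview gives 20 months of delivery, and 20 × 20 = 400. The two periods should be reconciled before the match is costed, but the algebra below does not depend on this.)

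**Plain reading: both costs over the one named effect.**

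- Combined: (X+G)/d2
- MFG-HIVSR plus FEE: X/d2, which has no interpretation, because d2 is not an effect of that arm
- Incremental ratio for the named contrast: [(X+G) − X]/d2 = G/d2
- Overstatement: [(X+G)/d2] ÷ [G/d2] = (X+G)/G, whatever d2 is

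**Illustration.** All values are assumed: X = 600, G = 100, d1 = 0.10, d2 = 0.05.

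| Quantity | Calculation | US $ |
|---|---|---|
| Combined, plain reading | 700/0.05 | 14,000 |
| MFG-HIVSR plus FEE, plain reading | 600/0.05 | 12,000 |
| Incremental, adding GED-HIVSR | 100/0.05 | 2,000 |
| MFG-HIVSR plus FEE against control | 600/0.10 | 6,000 |
| Combined against control | 700/0.15 | 4,667 |

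The overstatement here is 700/100 = 7-fold. Over assumed X of 480 to 800 and G of 50 to 200, it runs from (480+200)/200 = 3.4 to (800+50)/50 = 17. If G were as large as X, it would be 2.

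**The match alone.** It is paid in both intervention arms, so it contributes nothing to the incremental cost. On the plain reading it adds up to 480/d2 to the combined ratio: $9,600 at an assumed d2 of 0.05 and $4,800 at 0.10.

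**Alternative reading: each arm over its own effect against control.** The ratios are X/d1 and (X+G)/(d1+d2). Neither equals G/d2. With d1 of 0.05 to 0.15 and d2 of 0.03 to 0.10 over the same assumed costs, the combined-against-control ratio is 0.57 to 11.3 times the incremental one. It cannot stand in for the incremental ratio, and even the direction of the discrepancy is not fixed.

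**Scale.** Dividing an assumed cost of 600 by a relative risk of 1.1 gives 600/1.1 = 545. At an assumed control suppression of 60%, the risk difference is 0.60 × 0.1 = 0.06, and the cost per additional suppressed adolescent is 600/0.06 = 10,000.

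**The case against.** The strongest defence is that the effect sizes are plural, are called relevant, and come from analyses that include both comparisons with control (H1a and H1b). Each arm's cost may be meant to be divided by that arm's own effect. The ratios would then be sound on an absolute scale: only program costs are counted and bolstered usual care is given in every arm, so its cost cancels and X and X+G are already incremental to control.

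This stands as a possible reading, and it rules out some stronger inferences.

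- A reader might infer that Aim 3 is bound to report a wrong price, or that the control arm is left out. The text is not definite enough for either; both follow only on the plain reading.
- A reader might infer that costs will be divided by standardized differences. The outcome analyses do not produce them: Aim 1 gives relative risks and Aim 2 compares mean stigma. Standardized effects appear only in the power section.
- A reader might take a particular multiple as established. It is not, because the cost of GED-HIVSR (workshop, booster, school visits) is not stated.

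It is also fair that an article condenses. The resampling unit for the bootstrap, for example, can be left to a fuller document and is not part of this point. But the division rule is stated here, and the defence does not rescue it fully. The section names no contrast with control and no absolute scale, and on this reading too the rule does not yield the ratio for adding GED-HIVSR.

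**Conclusion.** The point holds in this form: on either reading, the stated rule does not produce the incremental price of adding GED-HIVSR, which is the question that the third arm was designed to answer. On the plain reading it also overstates that price by (X+G)/G. That factor is exact algebra and rests only on the two intervention arms sharing the MFG and FEE cost. Its numerical size is unknown; 3.4- to 17-fold is a range over assumed costs, and every dollar ratio above is illustrative.

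On the alternative reading the ratios against control are valid, provided that usual-care costs are equal across arms and effects are absolute. The second condition is not met as written, because the suppression model estimates a relative risk.

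The matter is confined to a secondary aim. It does not touch the primary comparison, the randomization or the sample size.

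**What to change.** Rewrite the ratio paragraph in the Aim 3 section so that each ratio is the difference in per-person cost divided by the difference in effect:

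1. MFG-HIVSR plus FEE against bolstered usual care: X/d1.
2. Combined against MFG-HIVSR plus FEE: G/d2.
3. Combined against bolstered usual care, shown in addition: (X+G)/(d1+d2).

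Define the effect as the model-standardized risk difference in viral suppression, obtained from the fitted Aim 1 model, rather than the relative risk. Build the planned Monte Carlo and bootstrap intervals on these incremental costs and effects.

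The cost is one rewritten paragraph before the economic analysis starts. Program costs and outcomes are already to be collected, so no new data are needed.

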### Data Analysis

#### Primary Analyses for Aim 1

To examine the effect of M-Suubi on HIV viral suppression, we hypothesize the following:

H1a: MFG-HIVSR plus FEE will have higher odds of viral suppression than control participants (bolstered usual care).H1b: MFG-HIVSR plus FEE plus GED-HIVSR will have higher odds of viral suppression than control participants.H1c: MFG-HIVSR plus FEE plus GED-HIVSR will have higher odds of viral suppression than MFG-HIVSR plus FEE.

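### Aim 3 puts confidence limits on a cost-to-effect ratio; limits formed in the usual percentile way lose their meaning whenever the effect's own 95% interval includes zero

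*Protocol article*

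**What the plan says.** The Aim 3 section of the protocol article fixes three things.

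- **Denominator.** "The outcome analyses described earlier will be used to estimate the extent to which" the combined arm improved outcomes such as viral suppression beyond MFG-HIVSR plus FEE alone. For viral suppression this is contrast H1c: "MFG-HIVSR plus FEE plus GED-HIVSR will have higher odds of viral suppression than MFG-HIVSR plus FEE".
- **Form of the estimate.** The per-person costs "will then be divided by the relevant effect sizes to produce estimates of cost-effectiveness".
- **Uncertainty.** "We will calculate CIs for point estimates using two methods: Monte Carlo [167] and bootstrap [168".

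The section does not say on which scale the effect enters the ratio. The primary analysis for Aim 1 works on a ratio scale: "a binomial distribution and log link will be used to fit a log-binomial model to estimate the relative risks". Nor does Aim 3 say what happens when the estimated effect, or part of its sampling distribution, is zero or negative.

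The design figures come from the power section: "we assume power=0.80, α=.05/3=.017, and 4 repeated assessments from 714 participants conservatively assuming 15% attrition", and "Standardized minimum detectable effect sizes range from .26 to .35".

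**The concern.** Program cost is positive, so the sign of the ratio follows the sign of the effect. As the effect shrinks to zero from above, the ratio grows without bound. Just below zero it is a very large negative number. The ratio is therefore not ordered in the way a confidence interval needs: the worst result (no gain for the money) lies in the middle of the effect distribution but at both extremes of the ratio distribution.

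Once draws fall on both sides of zero in more than small numbers, a percentile interval for the ratio has three faults:

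- It runs from a negative to a positive value.
- It contains a ratio of zero, which is impossible with a positive cost.
- It ends at a finite upper limit, although the data do not exclude an effect of zero.

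A policy reader would take that upper limit as the worst-case price per extra suppressed adolescent, when no such bound exists. Using two methods is no safeguard: if percentile limits are taken from both, Monte Carlo and bootstrap draws describe much the same distribution and show the same fault.

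**Working it through.** **Inputs from the power section:** power .80; alpha .05/3 per comparison; 840 × 0.85 = 714 analysed, which reproduces; detectable effects of .26 to .35 SD. That range cannot be uniquely reproduced, because the article gives no intracluster or within-person correlation. It is taken as stated. **Assumptions:** two-sided testing (the article does not say) and an approximately normal effect estimate.

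**Step 1. Detectable effect in standard errors.** z(1 − .05/6) + z(.80) = 2.394 + 0.842 = 3.236.

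**Step 2. When the limits break down.** With a positive cost, the 2.5th percentile of cost/effect is negative once more than 2.5% of effect draws are below zero, and the 97.5th is positive once more than 2.5% are above it. Both hold when the effect's own 95% interval includes zero, that is when the observed effect is within 1.96 SE of zero.

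**Step 3. In SD units.** SE = detectable effect / 3.236, which is .26/3.236 = .080 to .35/3.236 = .108. The threshold is 1.96 × .080 = .16 SD to 1.96 × .108 = .21 SD, below the design's own detectable effect in each case.

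**Step 4. How often.** If the true effect is a fraction f of the detectable effect, the observed z is normal with mean 3.236f and SD 1, and P = Φ(1.96 − 3.236f) − Φ(−1.96 − 3.236f).

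| True effect | Mean z | Probability that the limits span zero |
|---|---|---|
| Detectable effect (f = 1) | 3.24 | .10 |
| Half (f = .5) | 1.62 | .63 |
| A quarter (f = .25) | 0.81 | .87 |

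These probabilities do not depend on any cost figure.

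**Step 5. What the limits look like.** Illustration only: a cost of 100 with SE 5 is assumed, since the article gives no costs; the detectable effect is .26 SD.

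- Observed effect .26: ratio 100/.26 = 385, percentile limits about 236 to 970. These are usable.
- Observed effect .13: ratio 100/.13 = 769, percentile limits about −4,200 to 6,300. The figure of 6,300 is not a worst case, because the effect's interval is .13 ± 1.96 × .080, or −.03 to .29.

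**Step 6. The same data as net benefit.** For willingness to pay λ, net benefit = λ × effect − cost, with no division. At effect .13 and λ = 1,000 it is 130 − 100 = 30. Its SE, with cost and effect taken as uncorrelated, is √(80.4² + 5²) = 80.6, so the 95% limits are 30 ± 158, or −128 to 188. These limits are finite, correctly ordered, and show plainly that the data do not settle the question.

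**Step 7. Coverage.** Simulation with an assumed incremental cost of 300 (SE 20) and a detectable risk difference of .15 gives percentile coverage of about 97% at f = 1, .5 and .25, about 93% at f = .1 and about 82% at f = .05. For most of the range the fault is what the limits mean. Coverage itself fails only for very small effects.

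**The case against.** **The word percentile is not in the text.** Monte Carlo and bootstrap generate draws; how limits are formed from them could be set out in the cited references or in a fuller plan. This stands as a limit on the claim. The point is conditional on the usual percentile construction, and a reader should not infer that the article prescribes it or that the resampling is wrong. But the article does fix a ratio and does promise confidence limits on it, so the choice is stated and not merely left open.

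**The scale is not fixed.** A raw relative risk cannot reach zero, so the breakdown would not occur with it. That is true, but cost divided by a raw relative risk is not a cost per unit gained. Relative risk minus 1, its logarithm and the risk difference all have zero as the value for no effect.

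**The contrast could be read differently.** The heading refers to each condition and the text to effect sizes in the plural, so each arm's cost over its own effect against control is a possible reading. The sentence before the division names combined versus MFG-HIVSR plus FEE alone. Under either reading the arithmetic in step 4 applies to whichever effect is the denominator, because one detectable range is given for all hypotheses.

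**The added component must have a small effect for this to matter.** A reader might infer that H1c is expected to show the smallest effect. The article does not say so: it does not rank H1a to H1c by size. The point needs only that an effect below the detectable size is possible.

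**A non-significant H1c would warn readers.** Partly true, but the warning would sit elsewhere, while the ratio's upper limit would still be printed as a bound.

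**Conclusion.** The concern holds, within limits. On any effect scale where no effect is zero, percentile limits on the Aim 3 ratio cannot be interpreted when the effect's 95% interval includes zero. On the design's own power and alpha (two-sided assumed), the chance of this is about 10% at the detectable effect, 63% at half of it and 87% at a quarter. It is uncommon only when the true effect is at or above the detectable size.

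Three stronger readings are not supported: that the intervals always fail, that they generally under-cover, or that the bootstrap and Monte Carlo draws are faulty. The cost figures in the illustrations are assumptions; the probabilities are not affected by them. The matter is confined to Aim 3 and leaves the tests for Aims 1 and 2 and the sample size unchanged. It is worth correcting because the remedy is cheap and the misreading would concern the price of the program.

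**What to change.** Reword the end of the Aim 3 section as follows:

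1. State the effect as an absolute difference between arms, for example the risk difference in viral suppression.
2. Give the cost-effectiveness ratio as a point estimate only.
3. Express uncertainty from the same Monte Carlo or bootstrap draws, carrying cost and effect together, as incremental net benefit with confidence limits over a stated range of willingness to pay, plus a cost-effectiveness acceptability curve.
4. If Fieller limits on the ratio are wanted, report them always, including when they are unbounded. Reporting them only after a significant effect selects on the result: in the simulation set-up of step 7, coverage of the intervals actually reported was about 97% at the detectable effect, 93% at half and 78% at a quarter.

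The cost is one paragraph of text. No new data or extra resampling is needed. The downside is that the investigators must state and defend a willingness-to-pay range, preferably before outcome data are seen.
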